### Participants

Individuals who meet the following inclusion criteria will be recruited: (1) 18 years old or above; (2) admitted to the general medical and geriatric wards, ICUs, or subacute/rehabilitation/infirmary wards in subacute/convalescent/extended care hospitals or visiting AEDs in acute hospitals; and (3) requiring the insertion of an NGT into the stomach for assessment and monitoring, nutritional support, drainage, and medication administration during the study period. Individuals will be excluded from the study if they are receiving a life-saving intervention at the time of recruitment.

A convenience sampling method will be adopted in this study. The participants will be recruited in 39 wards/units across 21 acute or subacute/convalescent/extended care hospitals. Each participant will be included in the study once.

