#### Reference standard

The reference standard is the test, series of tests, or set of procedures used to determine the presence or absence of the target condition in individuals, which in this study is airway intubation of an NGT [25]. This study will use radiography (chest/abdominal X-ray) as the reference standard for determining the correct placement of NGTs. Radiology will be performed as soon as possible and interpreted by a physician. A repeat radiography will be performed if necessary. We will also use pH-Fix-4.5–10 to determine the pH value, and its accuracy is +/- 0.2 with minimum increments of 0.5. A pH of 5.5 or below indicates gastric placement [2].

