### Procedures

The principal investigators and co-investigators will provide two 1.5-hour training sessions to the designated nurses (DNs) at each study site, one e-learning session and one real-time synchronised online session. A DN is a registered nurse, advanced practice nurse, associate nurse consultant, or nurse consultant working in the study site. The training will cover principles, types, and clinical applications of capnography, representative capnographic waveform, limitations and issues of concern regarding capnography, the study protocol, procedures for ETCO_2_ detection using the bedside capnography device, and study documentation. All DNs must attend both training sessions and pass a 15-item quiz to demonstrate their knowledge of capnography monitoring. To ensure adherence to the study protocol, the project team will conduct non-participant observation once for each DN. The DN of each study site will assess participants’ eligibility based on the eligibility criteria, and no pre-screening by ward nurses will be performed to avoid selection bias.

Fig 1 depicts the flow of the participants and data collection procedures. Before insertion, the DN will set up the capnography device according to the manufacturer’s instructions, connect the Microstream Advance Adult-Pediatric Intubated CO_2_ filter line to the adapter, and then connect it to the CO_2_ input connector port on the monitor. The DN will check proper device function by placing the sampling port of the filter line at the nostrils for non-intubated patients or artificial airway for intubated patients and checking the capnography readings (i.e., observing the CO_2_ waveform and obtaining the ETCO_2_ reading).

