## Data analysis

The sample size is determined to give the study adequate precision to estimate the sensitivity and specificity of using capnography in detecting the placement of NGTs using the reference standards of measurement of radiography and aspirates for pH value. In anticipation of sensitivity and specificity of values greater than 90% [17], a sample size of at least 500 participants would be sufficient to estimate these parameters with a margin of error of at most ±3% at a significance level of 0.05. The sample size calculation was performed using PASS 16 (NCSS, Kaysville, USA). Eligible participants will be evenly recruited from the 39 participating wards/units. The target sample size will therefore be rounded up to 507 with 13 eligible participants per each of the 39 wards/units.

IBM SPSS 26.0 (IBM Crop., Armonk, NY) will be used to conduct the data analysis. Participants’ demographic and clinical characteristics will be presented by appropriate descriptive statistics, including mean ± standard deviation, median (inter-quartile range), and percentages for normally distributed, skewed continuous, and categorical variables respectively. Any cases with missing data on the index test or the reference standard results will be excluded from the test accuracy analysis. The true positives (i.e., NGT placements that are tested positive by both index test and reference test/s), false negatives (i.e., NGT placements that are tested negative by index test but positive by reference test/s), true negatives (i.e., NGT placements that are tested negative by both index test and reference test/s), and false positives (i.e., NGT placements that are tested positive by index test but negative by reference test/s) will be calculated, based on which the sensitivity, specificity, positive predictive value, and negative predictive value of the capnography test will be calculated with reference to a combination of X-ray and aspirate pH test using the following formulas:

$$\text{Sensitivity}:\;\text{True}\;\text{Positive}/\left(\text{True}\;\text{Positive}+\text{False}\;\text{Negative}\right)\times 100\%$$

$$\text{Specificity}:\text{True}\;\text{Negative}/\left(\text{True}\;\text{Negative}+\text{False}\;\text{Positive}\right)\times 100\%$$

$$\text{Positive}\;\text{Predictive}\;\text{Value}:\text{True}\;\text{Positive}/\left(\text{True}\;\text{Positive}+\text{False}\;\text{Positive}\right)\times 100\%$$

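### Convenience sampling with a quota of 13 per ward and no consecutive-enrolment rule leaves open which eligible insertions the designated nurse enrols

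*Protocol article*

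**What the plan says.** The Participants section of the protocol article gives the eligibility criteria and then the sampling rule: "A convenience sampling method will be adopted in this study". The Abstract repeats it. The Data analysis section asks for even recruitment over the sites, with the target "rounded up to 507 with 13 eligible participants per each of the 39 wards/units".

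The Procedures section has the designated nurse at each site assess eligibility against the criteria, and adds that "no pre-screening by ward nurses will be performed to avoid selection bias". No section says that eligible patients are enrolled consecutively, at random, or by any other fixed rule.

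Two further statements bear on the point. The Reference standard section names the target condition, "which in this study is airway intubation of an NGT". The Introduction justifies the study by the thin evidence in acute and rehabilitation settings, particularly general wards, emergency departments and intensive care.

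**The concern.** The authors recognise selection bias and act against it, but the safeguard reaches ward nurses only. After it, the designated nurse is the sole gatekeeper, with a small quota and no rule for which eligible patients fill it.

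The article itself shows how convenience could shape the sample. The designated nurse must be present before the tube is passed, to set up the device. Under Ethical considerations, a patient who lacks capacity can enter only after the next of kin has been contacted and has signed. Insertions that are urgent, out of hours, or in patients with impaired consciousness are therefore harder to enrol. That such insertions also enter the airway more often is plausible, but it is an assumption; the documents give no figure.

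Two things are at stake. The first is spectrum: the Data analysis section compares accuracy by consciousness, frailty, respiratory support, drug use and setting, and the Discussion expects the results to inform guidelines across the hospital authority. The second is the count of airway placements, since only these enter the denominator of sensitivity.

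**Working it through.** **Inputs from the article (Data analysis).** Anticipated sensitivity and specificity above 90%, with 0.90 taken as the worst case; margin of error at most 3 points; significance level 0.05; at least 500 participants; 39 wards or units with 13 each.

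**Inputs assumed.** The article gives no airway rate per insertion. Its figure of over 80% is the respiratory share of misplacements, not a rate per insertion. A range of 1% to 10% is used for the rate, and a range of 1 to 0.25 for the relative chance *r* that an airway-bound insertion is enrolled.

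**Step 1: the plan's own figure.** Wald: n = 1.96² × 0.90 × 0.10 / 0.03² = 384.2, so 385. Requiring the exact (Clopper-Pearson) lower limit to lie within 3 points of 0.90 gives 492. At n = 500 the Wald half-width is 2.63 points and the exact lower distance is 2.97 points. So 500 suffices when every participant counts towards the proportion. Then 500 / 39 = 12.8, rounded up to 13, and 39 × 13 = 507. The stated figures stand.

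**Step 2: expected airway placements without any selection.** At rates of 1%, 2%, 5% and 10%, 507 participants give about 5, 10, 25 and 51. The Wald half-width at 90% sensitivity, 1.96 × √(0.09 / m) for m airway placements, is about 26, 19, 12 and 8 points. Sensitivity rests on few cases even if enrolment is perfect.

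**Step 3: the same with selection.** If the true rate is π, the enrolled rate is πr / (πr + 1 − π). For π = 2% and r = 0.5 this is 0.010 / (0.010 + 0.980) = 1.01%, and 507 × 0.0101 = 5.1. The exact 95% lower limit with all m detected is 0.025^(1/m), with m rounded to a whole number.

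| True rate | r | Expected airway placements | Exact lower limit, none missed |
|---|---|---|---|
| 2% | 1 | 10.1 | 69% |
| 2% | 0.75 | 7.6 | 63% |
| 2% | 0.5 | 5.1 | 48% |
| 2% | 0.25 | 2.6 | 29% |
| 5% | 1 | 25.4 | 86% |
| 5% | 0.75 | 19.3 | 82% |
| 5% | 0.5 | 13.0 | 75% |
| 5% | 0.25 | 6.6 | 59% |

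Halving the enrolment of airway-bound insertions widens the half-width by about √2, or 1.4 times: from about 19 to 26 points at 2%, and from about 12 to 16 points at 5%.

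**Step 4: what the table does and does not show.** It shows lost precision. Sensitivity is conditional on airway placement, so enrolling fewer airway cases does not by itself shift the estimate. A shift would need the airway cases left out to be detected by capnography at a different rate from those enrolled. The documents allow no calculation of that.

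**The case against.** Several points on the other side stand.

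- A reader might infer that the sampling rule contradicts the safeguard. It does not. Barring ward-nurse pre-screening is compatible with an openly declared convenience sample; the protection is incomplete, not inconsistent.
- A reader might infer that the designated nurse is permitted to pick easy cases. No section says so; the nurse applies the eligibility criteria. What the text supports is that the order of enrolment among eligible patients is not fixed.
- A reader might infer that airway cases can be dropped as such. Consent and device set-up come before insertion, so tube position is unknown at enrolment. Any loss is indirect, through patient risk and nurse availability.
- A reader might divide 13 by two years of insertions to measure the nurse's freedom. The Study duration section gives two years for the research as a whole and only a start month for data collection, so the recruitment period is not stated. Insertions with no designated nurse on duty, repeat insertions and refusals would also sit in that denominator.
- Even recruitment over 39 wards and units, including intensive care and emergency departments, already protects the mix of settings. It does not protect the mix of patients within a ward.
- Small numbers of airway placements are a problem without any selection, as Step 2 shows. Selection can only add to it.
- A condensed article may leave a screening log to the full protocol, so its absence is not held against the plan. Nor could the participant-flow figure be read here.

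None of this removes the core point, because convenience sampling is a stated design choice and not an omitted detail.

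**Conclusion.** The point holds in a limited form. The article fixes convenience sampling with a ward quota and states no consecutive rule, so selection among eligible insertions stays open at the level of the designated nurse despite the bar on ward-nurse pre-screening. The patient spectrum may be narrowed, and the airway placements that carry sensitivity may be fewer.

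Neither the size nor the direction of any bias in sensitivity or specificity can be derived. The falls in the lower limit illustrate precision only, and rest on assumed airway rates and an assumed selection ratio. They are not estimates for this study. The change is worth making because it is cheap and completes a protection that the authors already intend.

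**What to change.** In the Participants section, replace convenience sampling with consecutive enrolment. From a fixed start date, the designated nurse approaches every eligible patient who needs a nasogastric tube while that nurse is on duty, until the ward reaches 13. Each eligible on-duty patient who is not enrolled is recorded with the reason.

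The target stays at 507 and no test or procedure is added. The cost is that the designated nurse loses discretion over timing and takes on some extra consent and recording work, including contact with next of kin. The rule removes on-shift discretion only. Insertions outside designated-nurse shifts remain uncovered, and the article should state this as a limitation.

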### Test methods

#### Index test

Capnography, which monitors ETCO_2_, the percentage concentration, or partial pressure of CO_2_ at the end of exhalation, will serve as the index test. It will be performed by connecting the end of the NGT with the sensor of the bedside sidestream capnography device (Medtronic Capnostream 35 Portable Respiratory Monitor) through an adapter [22]. After connecting the NGT to the sensor, the ETCO_2_ level should be read after a minimum of six breaths or one minute to avoid confusion resulting from CO_2_ in the stomach [13,18,23,24]. Placement within the airway is defined as detecting a capnogram waveform or an ETCO_2_ level > 15 mmHg (2.0 kPa) [15].

#### Reference standard

The reference standard is the test, series of tests, or set of procedures used to determine the presence or absence of the target condition in individuals, which in this study is airway intubation of an NGT [25]. This study will use radiography (chest/abdominal X-ray) as the reference standard for determining the correct placement of NGTs. Radiology will be performed as soon as possible and interpreted by a physician. A repeat radiography will be performed if necessary. We will also use pH-Fix-4.5–10 to determine the pH value, and its accuracy is +/- 0.2 with minimum increments of 0.5. A pH of 5.5 or below indicates gastric placement [2].

### Procedures

The principal investigators and co-investigators will provide two 1.5-hour training sessions to the designated nurses (DNs) at each study site, one e-learning session and one real-time synchronised online session. A DN is a registered nurse, advanced practice nurse, associate nurse consultant, or nurse consultant working in the study site. The training will cover principles, types, and clinical applications of capnography, representative capnographic waveform, limitations and issues of concern regarding capnography, the study protocol, procedures for ETCO_2_ detection using the bedside capnography device, and study documentation. All DNs must attend both training sessions and pass a 15-item quiz to demonstrate their knowledge of capnography monitoring. To ensure adherence to the study protocol, the project team will conduct non-participant observation once for each DN. The DN of each study site will assess participants’ eligibility based on the eligibility criteria, and no pre-screening by ward nurses will be performed to avoid selection bias.

Fig 1 depicts the flow of the participants and data collection procedures. Before insertion, the DN will set up the capnography device according to the manufacturer’s instructions, connect the Microstream Advance Adult-Pediatric Intubated CO_2_ filter line to the adapter, and then connect it to the CO_2_ input connector port on the monitor. The DN will check proper device function by placing the sampling port of the filter line at the nostrils for non-intubated patients or artificial airway for intubated patients and checking the capnography readings (i.e., observing the CO_2_ waveform and obtaining the ETCO_2_ reading).

**Fig 1 pone.0292667.g001:**
[figure not shown]
The flow of participants and data collection procedures in the study. This is the Fig 1 legend. (Abbreviation: DNs: Designated nurse(s) of the study venues; ETCO_2_: End-tidal carbon dioxide; ID: Identity; NGT: Nasogastric tube).

Ward nurses in the study site responsible for insertion of the NGT will estimate the distance to placement using the nose-earlobe-xiphoid (NEX) measurement and then insert the NGT according to the standard clinical practice guideline of the Hospital Authority Hong Kong (without connecting the capnography device at this point). The NGT used in all cases will be either a large bore NGT or a fine bore NGT. When the tube is advanced to a distance determined by the NEX method, ward nurses will inject and draw air with a 20 or 60 mL irrigation syringe to ensure tube patency and check if the NGT is not coiled inside the oral cavity.

Afterward, the DN will perform the index test (monitoring the ETCO_2_ using the capnography device) independently in the absence of the nurse who inserted the NGT in the following manner: i) Connect a new 20 or 60 mL syringe to the NGT and flush in 10 mL of air to clear any blockage; ii) Remove the syringe, connect the capnography device to the distal end of the NGT (by firmly connecting the device, the filter line with adapter and the NGT); iii) Check for any capnographic waveform and ETCO_2_ reading after a minimum of six breaths or one minute, whichever is longer, and record the results. To minimise bias in the study, the DN will not disclose the results of ETCO_2_ detection to the related ward nurses, participants, radiographer, or the physicians/radiologists who will interpret the X-ray imaging.

The ward nurses will independently aspirate gastric contents for pH measurement and report the pH value to the DN for record. The procedure will be stopped immediately if participants show signs of respiratory intolerance, such as repeated vigorous cough or cyanosis [26]. Then the patient will be arranged to receive a chest/abdominal X-ray. The DN will trace the X-ray results, which will then be interpreted by a physician (blind to the result of the index test) to confirm the position of the NGT. Enteral feeding (if prescribed) will begin once the position of the NGT is confirmed, otherwise, the NGT will be withdrawn and re-inserted according to the protocol.

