An increasing amount of evidence suggests that end-tidal carbon dioxide (ETCO_2_) detection may be a promising method to verify NGT placement [2,6]. Capnography comprises the continuous analysis and recording of CO_2_ in respiratory gases. The placement of the NGT within the airway is defined as the detection of ETCO_2_ levels exceeding 15 mmHg (2 kPa) [12–15]. An NGT is also considered to be placed in the respiratory tract if a change from purple to yellow is detected by a colorimetric ETCO_2_ device [14]. We conducted a meta-analysis of nine studies involving 651 NGT placements and found that the pooled results for sensitivity and specificity of ETCO_2_ detection in differentiating respiratory and gastrointestinal (GI) placement of NGTs among critically ill adult patients were high, both of which were 0.99 [16]. After a comprehensive search of databases from 2009 to March 2021, the review was updated, and seven new studies were identified. Of the 16 included studies with 1,878 NGT placements, the pooled results for sensitivity and specificity were 0.96 and 0.99, respectively [17]. The results consistently suggest that capnography and colorimetric capnometry may be of comparable diagnostic accuracy to radiography in their ability to differentiate between respiratory and GI tube placement in critically ill adult patients. However, the limited number of studies conducted in general wards and other hospital settings renders the determination of diagnostic accuracy in this patient population uncertain [13,18].

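### Masking of the capnography result has no stated end, and no step is given for a positive capnogram that disagrees with an X-ray read as gastric

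*Protocol article*

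**What the plan says.** All of the key statements are in the Procedures section of the protocol article, in the text after the Fig 1 legend.

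- **Non-disclosure.** After the index test, "the DN will not disclose the results of ETCO_2_ detection to the related ward nurses, participants, radiographer, or the physicians/radiologists". The sentence goes on to limit the last group to those who interpret the film. The stated reason is "To minimise bias in the study". No end point or exception is given.
- **Order of tests.** Capnography comes first, then the ward nurses' pH measurement. After that, "Then the patient will be arranged to receive a chest/abdominal X-ray". The film is "interpreted by a physician (blind to the result of the index test) to confirm the position of the NGT".
- **Stop rule.** "The procedure will be stopped immediately if participants show signs of respiratory intolerance, such as repeated vigorous cough or cyanosis". This rests on clinical signs, not on the capnogram.
- **Feeding.** "Enteral feeding (if prescribed) will begin once the position of the NGT is confirmed"; if the position is not confirmed, the tube is withdrawn and re-inserted.

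Under Data collection, the DN records the capnography result and follows up the pH and X-ray results on the same form. Under Reference standard, radiography may be repeated when needed.

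**The concern.** Masking the X-ray reader and the nurses who measure pH is sound design. The difficulty is that the sentence sets no limit in time. The DN is the one person in the described procedure who is certain to see all three results, yet the text gives that person nothing to do when a positive capnogram meets a film read as gastric. Followed literally, the DN records the disagreement and says nothing to anyone on the list.

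The Introduction states that tubes placed in the respiratory tract can lead to serious lung complications. A positive capnogram is not proof of airway placement, but it is relevant to that risk. If withholding it no longer serves the analysis, there is no methodological reason to go on doing so.

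**Working it through.** **Step 1. What the masking protects.** The analysis cross-classifies the capnography result against the X-ray and pH reference (Data analysis section). Knowledge of the capnogram could affect three things:

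- the pH reading, until the ward nurses have reported the value;
- the X-ray reading, until the physician's interpretation is documented;
- a repeat film, if it is ordered or read after disclosure.

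The capnogram is recorded before any of these. Once the pH and the blinded reading are also recorded, the participant's cell in the two-by-two table is fixed, provided that no reading made after disclosure enters the reference. With that proviso, later disclosure cannot change sensitivity, specificity or the predictive values.

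**Step 2. Whether another safeguard uses the capnogram.** Going through the text:

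- Stop rule: triggered by signs of intolerance.
- pH measurement: made independently of the capnogram.
- Repeat radiography: allowed when needed, with no link to the capnogram.
- Withdrawal and re-insertion: triggered when the position is not confirmed.

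Each is a real safeguard, but none is linked to the capnogram.

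**Step 3. The burden of releasing the result.** Inputs from the article are n = 39 × 13 = 507, which reproduces the stated target, and pooled sensitivity 0.96 and specificity 0.99 (Introduction). The Introduction gives no rate of airway placement per insertion, so 1% to 10% is assumed. The reference is taken as error-free in this step.

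- Airway tubes D = 507 × rate
- True positives = 0.96 × D
- False positives = (1 − 0.99) × (507 − D)
- Positive predictive value = true positives / (true positives + false positives)

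| Assumed rate | Airway tubes | True positives | False positives | PPV |
|---|---|---|---|---|
| 1% | 5.07 | 4.87 | 5.02 | 49% |
| 2% | 10.14 | 9.73 | 4.97 | 66% |
| 5% | 25.35 | 24.34 | 4.82 | 83% |
| 10% | 50.70 | 48.67 | 4.56 | 91% |

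False positives stay at about 5, or 5/507 = 1.0% of participants, across the range. These tubes are not in the airway, so the figure measures the review burden, not harm prevented.

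**Step 4. The number that would measure the benefit.** This is the count of airway tubes with a positive capnogram and a film misread as gastric: true positives × misreading rate m. The documents give no m. Assuming 0.5% to 10%, independent of the capnogram:

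- lowest: 4.87 × 0.005 = 0.024 tubes
- highest: 48.67 × 0.10 = 4.87 tubes

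The chance of at least one is 1 − (1 − rate × 0.96 × m)^507. This runs from 1 − (1 − 0.000048)^507 = 2.4% to 1 − (1 − 0.0096)^507 = 99.2%. The range is too wide to support any estimate.

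**The case against.** The best reply is that this is an omission in a condensed article, not an error. Fig 1 sets out the participant flow and is not shown, and a release rule could sit there or in the full protocol. That stands as a limit: the point concerns the text as printed. But the printed sentence fixes the masking without qualification, and stating its end is a specific improvement.

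A second reply is that disclosure could damage the reference standard. Repeat films are allowed, and re-checking the reference only where the index test is positive is differential verification. This is right, and it is why readings made after disclosure must stay out of the reference.

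A reader might infer several stronger points that the documents do not support:

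- **That the protocol contradicts its Introduction.** The Introduction says that capnography and colorimetric capnometry "may be of comparable diagnostic accuracy to radiography in their ability to differentiate between respiratory and GI tube placement". That is hedged and confined to critically ill adults, and the next sentence calls accuracy in other hospital settings uncertain. Not acting on a test under evaluation is consistent with it.
- **That the stop rule is the only protection.** pH testing, repeat radiography and withdrawal of an unconfirmed tube are also described.
- **That the whole treating team is barred permanently.** The text is silent on duration, and a physician who does not read the film is not on the list.
- **That the roughly 5 discordant participants are the ones at risk.** They are expected capnography false positives.
- **That an X-ray read as gastric settles classification.** The analysis combines X-ray with pH.

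**Conclusion.** The point holds as a modest, cheap improvement. The text shown gives no end to the masking and no step for discordance between capnogram and X-ray. The bias rationale is exhausted once the pH and the blinded X-ray reading, including any repeat film taken before disclosure, are on record. Withholding after that adds no validity and leaves a safety-relevant signal unused.

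The masking up to that point is not at fault. It cannot be concluded that airway tubes will be fed through: that would need an X-ray error that the other safeguards also miss, and its frequency cannot be estimated from the documents. The one figure that is stable is the review burden of about 5 of 507 participants, which rests on the cited specificity of 0.99 carrying over to this population. The conclusion also assumes that neither Fig 1 nor the full protocol already states a release rule.

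**What to change.** - State in Procedures that non-disclosure ends once the pH value and the blinded X-ray reading are documented, and add a time stamp for that moment to the data collection form.
- State that only pH values and X-ray readings made before disclosure form the reference standard. A film taken or read afterwards may be reported but does not reclassify the participant.
- List participants with a positive capnogram and an X-ray read as gastric descriptively.
- The sponsor should reconcile the non-disclosure sentence with the stop rule and the feeding sentence, so that the DN knows how a discordant result is handled. Any clinical action is for the sponsor and sites to decide.
- Because the list depends on what counts as positive, reconcile the ETCO2 threshold as well: above 10 mmHg in the Abstract, above 15 mmHg under Index test.

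The cost is a few sentences in Procedures, one field on the form and a line in DN training. The downside is possible delay in tube use while a disagreement is reviewed, in about 5 of 507 participants who would be capnography false positives. If Fig 1 or the full protocol already holds a release rule, carrying it into the text is enough for the first item.
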